#### Projected quit rates

As defined in the 2012 Cochrane review of smoking cessation in hospitalized patients [35], across both study arms, smokers who receive post-discharge support and medications will receive level-4 intensity treatment and smokers who receive only inpatient brief counseling will receive level-1 intensity treatment. Pooled quit rates are 10% for level-1 intensity studies and 29% for level-4 intensity studies [35]. Based on EQUIP and other trials, we estimate that 30% of OPT-IN participants will be ready to quit and receive services [36, 37]. For OPT OUT, based on the Inter99 trial and our pilot study on proactive quitline counseling we estimate that 80% of patients will accept services [38, 39]. We calculate the proposed quit rates within each condition using the following formula:$$ \left[\left(\mathit{\mathsf{prop}}.\mathit{\mathsf{receivingservices}}\times \mathit{\mathsf{level}}\ \mathit{\mathsf{4}}\ \mathit{\mathsf{quitrates}}\right)+\left(\mathit{\mathsf{prop}}.\mathit{\mathsf{not}}\ \mathit{\mathsf{receivingservices}}\times \mathit{\mathsf{level}}\ \mathit{\mathsf{1}}\ \mathit{\mathsf{quitrates}}\right)\right]. $$

We estimate the quit rate to be 15.7% in the OPT-IN group: [(.30 × .29) + (.70 × .10)] = .157. We estimate the quit rate to be 25.2% in the OPT-OUT group: [(.80 × .29) + (.20 × .10)] = .252.

#### Power, sample size, and trial duration

In accordance with guidelines for adaptive design power analyses [34], we used simulated data to determine the power, sample size, and anticipated duration of the study. We created virtual responses for our “expected” quit rates, another for “small but unlikely” quit rates, and a third for “no differences” in quit rates. We performed three sets of trial simulations (Table 4). Each set involved many trial simulations that identified power (the probability of success) in two scenarios—one for early success (i.e., being able to stop randomization early) and one for late success (i.e., upon enrolling all 1000 patients). While two of these combinations are very unlikely to occur, we included all scenarios. First, under the “expected” quit rates, we estimated (identified) that 92% of the simulated trials had early success, 3% late success, and only 5% had incomplete results. Thus, this scenario had 95% power. The average sample size of this trial scenario was 625 patients with more than half (387) in the better OPT-OUT arm. The average length of these simulated trials was 98 weeks. Second, if there are “small but unlikely” quit rates, we identified that 30% of the simulated trials had early success, 5% had late success, and 65% had incomplete results. This trial scenario had 35% power and the sample size of this trial scenario was on average 903 with more than half (530) in the better OPT-OUT arm. The average length of this trial scenario was 142 weeks. Third, we examined the scenario that serves as our null hypothesis. In this scenario there are no differences in quit rates among the arms. The extent to which this scenario is “successful” reflects our Type-I error rate. For this scenario, we identified that 4% of the simulated trials had early success, 1% late success. This trial scenario produced an appropriate expected Type-I error (*α* = .05). The sample size of this scenario on average was 986 patients, with about half (495) in the OPT-OUT arm. The average length of the trials under this scenario was 155 weeks—approximately 3 years of recruitment. Hence, our maximal sample size of 1000, in 3 years of recruitment, provides ample time and participants to identify project outcomes under all three scenarios.

**Table 5 Tab5:** Study hypotheses, measures, and analytic strategy

Purpose	Variables	Analytic strategy
Hypothesis 1: compared to OPT IN, significantly more patients in OPT OUT will participate in counseling, use cessation medications, and be abstinent from smoking	Abstinence: treatment condition and 1-month 7-day point-prevalence abstinence	2-sample binomial test
	Counseling: treatment condition and total counseling time by 1 month	2-sample lognormal test
	Medication: treatment condition and number of days of medication use	2-sample Poisson test
Hypothesis 2: significantly more smokers in OPT OUT will be abstinent from smoking, and mediation analyses will partially or fully explain the effects	Treatment condition and 6-month and • 7-day point-prevalence abstinence • Default variables • Counseling/medication use	Bayesian structural equation modeling with a logistic outcome
Hypothesis 3: OPT OUT will be more costly but also more effective than OPT IN	Treatment condition and 1-month abstinence • Variable costs	Incremental cost/quit

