### Study procedures

The study employs a modified Zelen design for consent [17, 18]. Study staff will select, randomize, and intervene with patients prior to collecting verbal consent at the 1-month post-discharge visit. For the outcome analysis, the study uses a Bayesian adaptive trial design [19]. Mediation analyses will also provide insight into why changing the default did, or did not, work. We hypothesize that smoker perceptions of what course of action their cessation counselor recommends, and what is the status quo for receiving medications and counseling at the hospital, will affect their counseling participation, medication use, and quit rates (Fig. 1). The trial will be implemented in four stages over 4.5 years (Table 1).

**Table 1 Tab1:** Clinical trial timeline

Month	Stage	Milestones (by end of year, unless otherwise stated)
6–23	1: Early implementation	• 400 participants consented • 6-month outcome data collected on 200 participants • Manuscript on study design under review
24–39	2: Implementation	• Baseline data collected on 800 participants • 6-month data collected on 600 of participants • Data cleaned and prepared for analysis on half of all participants
40–51	3: Early analyses	• Complete consent of final 200 participants by midyear • 6-month data collection completed on all participants • Manuscripts on baseline characteristics of participants published
52–60	4: Analysis/dissemination	• All data cleaned and prepared for analysis • Conduct all outcome, mediator/moderator analyses • Manuscripts on study outcomes under review

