#### Bayesian design

We will perform a prospective randomized comparative effectiveness *Bayesian adaptive design study* [34]. Our endpoint is the percentage of patients with verified cessation at 1 month (4 weeks) post randomization. We will perform our first planned interim analyses when we have endpoint data on 400 patients. The arm that appears to be performing the best will get more participants allocated to it in the subsequent randomization period. A new adaptive randomization structure will be updated every 13 weeks, using up-to-date outcome data, until the trial meets success or all 1000 subjects are consented. The main outcome analysis will use an ITT approach, with the denominator being all participants randomized to the study. Data from patients we are unable to reach at 1 month will be de-identified and included in data analyses.

For this study the primary endpoint is modeled:
*S*
_*QjT*_|*n*
_*jT*_ ~ Bino(*n*
_*jT*_
*,θ*
^*Q*^
_*j*_) quitting.

In addition, we provide “weakly informative” priors:logit(*θ*
^*Q*^
_*j*_) ~ N(0,100^2^).

Using the endpoint data and the prior probabilities, we then use Markov Chain Monte Carlo computations to obtain the Bayesian posterior distributions for the endpoint (i.e., quitting). We will stop randomizing into the comparative trial if the probability of a study arm having maximum utility is greater than 0.9925. The arm having the maximum quit rate is *M*
_*T*_ = max(*θ*
^*Q*^
_*1,*_
*θ*
^*Q*^
_*2*_). The stopping rule is mathematically *P*(*M*
_*T*_ > .9925). If a maximum arm is not identified after 500 patients, this procedure and accrual will continue until a maximum arm is identified or we enroll all 1000 patients. It is possible that we will reach the maximum utility criterion before 1000 patients are consented. Should this occur, we will stop the trial and begin outcome, cost, and mediation analyses in order to quickly disseminate findings.

After the maximum arm probability is evaluated, the next round of patients is randomized using a formula that favors the arm with the maximum quit rate, thus taking advantage of the information gained from our interim analyses. Using this formula, each arm is allocated for the next patients to be enrolled in the *j*
^th^ arm proportional to:$$ {V^{\ast}}_j=\mathrm{sqrt}\Big(\Pr \left({M}_{jT}={\theta^Q}_1\Big)\mathrm{Var}\left({\theta^Q}_1\right)/\left({n}_{jT}+1\right)\right). $$

This type of allocation has more desirable properties than simply using Pr(*M*

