#### Analyses by aim

The main analyses for each aim are outlined below (Table 5).

Aim 1. Hypothesis 1: among patients consented into the trial, significantly more patients in OPT OUT will participate in counseling, use cessation medications, and be abstinent from smoking at 1 month post randomization compared to OPT IN. These analyses will involve two-sample tests.

Aim 2. Hypothesis 2: significantly more smokers in OPT OUT will be abstinent from smoking, and mediation analyses will find that counseling participation, medication use, and default-theory-based variables will partially or fully explain the effect of OPT OUT on cessation at 6 months post randomization. After identifying a structural equation model that adequately fits the data for the hypothesized associations between the intervention and 6-month outcome, i.e., that Comparative Fit Index (CFI) > .9 and Root Mean Square Error of Approximation (RMSEA) < .8, we will examine mediation using approaches based on the work of MacKinnon et al. [49], Brown [50], and Shrout and Bolger [51]. Our theoretical model (Fig. 1, Significance) will guide our analysis.

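### Table 5 and Aim 1 test the primary abstinence hypothesis for significance, in consented patients, without tying that test to the posterior rule for which the 5% type I error was simulated

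*Protocol article*

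**What the plan says.** The protocol article describes the analysis of the primary endpoint, verified 7-day abstinence at 1 month, in two ways.

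**The posterior rule.** Study procedures states: "For the outcome analysis, the study uses a Bayesian adaptive trial design". The Bayesian design section models quitting as binomial in each arm with a very diffuse normal prior on the logit. It then sets the stopping threshold: "We will stop randomizing into the comparative trial if the probability of a study arm having maximum utility is greater than 0.9925". The finding is to be confirmed at a posterior probability above 0.99 once all enrolled patients have data. On the population it says: "The main outcome analysis will use an ITT approach, with the denominator being all participants randomized to the study". The power section counts only this rule as success. It reports 4% early plus 1% late success when the arms do not differ, and concludes: "This trial scenario produced an appropriate expected Type-I error".

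**The two-sample test.** Table 5, Hypothesis 1, says that "significantly more patients in OPT OUT will participate in counseling, use cessation medications, and be abstinent from smoking". For abstinence it names a "2-sample binomial test". In Analyses by aim, Aim 1 places the hypothesis "among patients consented into the trial" and adds: "These analyses will involve two-sample tests". Neither place gives a significance level, a sidedness or a threshold, and neither refers back to the posterior rule, the interim looks or the adaptive allocation.

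**The concern.** One endpoint has a fully specified decision rule in one section and an unlinked significance test in another. The populations differ too: all randomized participants for the rule, consented patients for the test. An analyst who took Table 5 and Aim 1 at their word could run an ordinary two-sample test on the final data. That test would ignore about seven interim looks and the outcome-driven allocation, and nothing in the article gives its error rate. A trial that the power section would class as incomplete could then be reported as showing significantly more quitters under OPT OUT.

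**Working it through.** **Inputs, all from the protocol article**
- Quit rates of 15.7% in both arms (null), 15.7% v 20.0% (small effect) and 15.7% v 25.2% (expected): Table 4 and Projected quit rates.
- First look at 400 patients with endpoint data, updates every 13 weeks, maximum 1000, 4-week endpoint: Bayesian design.
- Poisson accrual, mean 6.7 per week: Accrual patterns.
- Stop above 0.9925 for either arm; final criterion above 0.99: Bayesian design.
- Allocation 1:1 at first, then proportional to sqrt(Pr(arm is best) × Var / (n + 1)), with the printed formula read as arm-specific.

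**Number of looks.** Each interval brings 13 × 6.7 = 87.1 patients, and (1000 − 400) / 87.1 = 6.9, so there are about seven looks.

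**Thresholds on one scale.** With a near-flat prior, Pr(θ1 > θ0) ≈ Φ[(p1 − p0) / sqrt(v1 + v0)], where p is the observed quit rate and v its posterior variance. At a single look:
- posterior 0.9925 corresponds to z = 2.43;
- posterior 0.99 corresponds to z = 2.33;
- a conventional two-sided 0.05 test needs z = 1.96 and is therefore looser.

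**Reproducing the plan's own figures.** The simulation used 20,000 null trials and 6,000 for each alternative. Its main setting was a first look at 400 with the 4-week lag.

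| Scenario | Stated success | Simulated, with final confirmation | Simulated, without it |
|---|---|---|---|
| Null | 5% (4 + 1) | 4.9% (4.3 early + 0.7 late, before rounding) | 5.6% |
| Small | 35% | 32.9% | 35.6% |
| Expected | 95% | 90.2% | 93.2% |

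The 5% type I error is reproduced. The expected-effect power comes out a little below the stated figure, which does not affect this point.

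**Adding the assumed test.** A pooled two-sample z test at two-sided 0.05 was applied to the same final data. Every trial that met the posterior rule was also significant, so the discordant share is a simple difference:
- Null: 7.29% − 4.91% = 2.38%.
- Small: 42.83% − 32.85% = 9.98%.
- Expected: 95.87% − 90.22% = 5.65%.

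**Robustness.**
- A second implementation, with exact Beta posteriors and 12,000 trials per scenario, gave 6.7% for the test against 4.7% for the rule under the null. Significance with the rule unmet occurred in about 2%, 9% and 4% of null, small and expected trials.
- A third run gave 7.4% against 4.9%, with 2.5%, 10% and 6%.
- Variants without the data lag, with a first look at 500, or without adaptive allocation put the test's type I error between 6.6% and 7.5%.
- Over those variants, and also without the final confirmation, the discordant shares ran from 1.4 to 2.7% (null), 7 to 10% (small) and 3 to 6% (expected).

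**Population.** The article gives no expected refusal rate for this trial, so the effect of restricting to consented patients is not quantified here. The two descriptions conflict whatever its size.

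**The case against.** The strongest reply is that there is only one criterion. Table 5 is a condensed summary, and its binomial, lognormal and Poisson labels can be read as naming the likelihood for each endpoint. The posterior model is itself a comparison of two binomial samples, and Study procedures says the outcome analysis is Bayesian. The word significantly does not prove a frequentist test, because Hypothesis 2 uses it beside an explicitly Bayesian structural equation model. The exact form of a test may also be left to a fuller document.

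Much of this stands. A reader might infer that the protocol sets two competing success criteria with different error rates, or that its claimed 5% type I error is wrong. The documents support neither inference. A threshold and an error rate are attached only to the posterior rule, the 5% for that rule reproduces, and the two-sided 0.05 level used above is an assumption.

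The reply does not remove the mismatch:
- The overview of analyses says Bayesian analysis drives allocation and then lists outcome analyses as an addition.
- The Bayesian design section has outcome analyses begin after the stopping criterion is met, which reads as a separate later step.
- Table 5 writes Bayesian for Hypothesis 2 and omits it for Hypothesis 1.
- Aim 1 names a different population from the main analysis, so as written the two are not the same analysis.

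This is therefore more than detail left to another document. The article gives both descriptions, and they do not match.

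**Conclusion.** The point holds as an unlinked and undefined test in Table 5 and Aim 1, together with a conflict of populations. If the test is the Bayesian binomial comparison at the stated thresholds in all randomized participants, there is one criterion with a type I error of about 5%, and only the wording needs repair. If it is run as a conventional unadjusted two-sided 0.05 test, the inflation is modest, about two percentage points over the rule. The disagreement then runs only towards extra positive claims and is most frequent in the small-effect scenario. These sizes rest on the assumed level and sidedness, on the arm-specific reading of the allocation formula, and on applying the test to the same final data as the rule.

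**What to change.** In Table 5 and under Aim 1, state that the Hypothesis 1 abstinence claim rests only on the posterior rule in the Bayesian design section (above 0.9925 to stop, above 0.99 at the final evaluation). State that it is assessed in all randomized participants, and reconcile the consented-patients wording of Aim 1 with this. Report the posterior difference in quit rates with its credible interval. Delete any other two-sample test of abstinence, or label it descriptive with no significance claim, and treat any consented-only analysis of abstinence the same way. The two-sample models for counseling time and medication days can stay as secondary analyses.

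The cost is about two lines of wording, with no change to the design, sample size or data collection. The criterion is slightly stricter than a nominal 5% test (z of about 2.33 to 2.43 rather than 1.96), but it is the one on which the stated power already rests.

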#### Inpatient counseling and treatment plan—OPT IN

For patients in OPT IN, staff will screen for willingness to stay having quit after leaving the hospital. Patients who are willing to quit will be offered similar counseling, treatment planning, and medications as patients in OPT OUT, including a pamphlet with tips on quitting. However, instead of proactively providing these services, staff will ask patients if they would like each element of the treatment plan—post-discharge counseling and/or post-discharge prescription for medication. Patients will only receive the elements of care to which they opt in.

Patients in OPT IN who are not willing to quit will receive brief intervention, in accordance with current treatment guidelines. This consists of a four-page pamphlet with resources for quitting and a brief counseling session that addresses the “5 Rs” of motivational counseling (*Relevance, Risks, Rewards, Roadblocks, Repetition*) [3].

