#### Post-discharge treatment—OPT OUT—counseling

All patients in OPT OUT will be enrolled in post-discharge counseling that will be delivered by study staff. Participants who accept enrollment into counseling services will receive up to four proactive counseling calls in each of the 4 weeks following discharge. Each call is designed to provide practical counseling to help participants develop problem-solving and coping skills, secure social support, and design a plan for successful cessation and long-term abstinence. Initial calls last approximately 30 min and follow-up calls last on average 15 min. Once participants quit smoking, counselors review high-risk situations, coping skills, and stress management to prevent relapse. When participants “slip,” counselors troubleshoot relapse situations and encourage smokers to quit again. We will use RedCAP to store data for all calls, including number of attempts to reach the smoker, number of calls completed, and duration of calls.

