#### Secondary outcomes, mediators, and moderators

Study counselors will track counseling data, which will be summarized as “total counseling time” for analyses. We will assess the type, the dose, and the number of days of medication was used via the method of Williams et al. [31, 32]. This will be summarized as “number of days of medication use” for analyses. Default-related variables are derived from the academic literature on choice theory and include smokers’ perceptions of provider attitudes toward tobacco-cessation treatment (implied recommendation), smokers perceptions of the degree to which their provider recommends tobacco-cessation treatment (implied recommendation), perceptions of the “status quo” for hospital tobacco-cessation treatment (status quo bias), and perceptions of paternalistic treatment by UKanQuit staff [13, 23, 33].

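### Hypothesis 1 claims that more OPT OUT patients take part in counselling, but the only test named for it compares total counselling minutes on a lognormal scale, which does not measure participation

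*Protocol article*

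**What the plan says.** The protocol article states under Analyses by aim, and again in Table 5, that "significantly more patients in OPT OUT will participate in counseling". In Table 5 the counselling row of Hypothesis 1 lists "treatment condition and total counseling time by 1 month" as the variable and a "2-sample lognormal test" as the analysis. The abstinence row of the same hypothesis uses a two-sample binomial test.

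The section on secondary outcomes, mediators and moderators says "Study counselors will track counseling data" and that these data are summed as a total time. It gives no rule for patients with no minutes, and it does not say whether time spent in hospital counts.

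On uptake, the section on projected quit rates says "we estimate that 30% of OPT-IN participants will be ready to quit and receive services" and, for OPT OUT, "we estimate that 80% of patients will accept services". The post-discharge sections tie calls to acceptance. For OPT OUT, "Participants who accept enrollment into counseling services will receive up to four proactive counseling calls"; for OPT IN, "Patients will only receive the elements of care to which they opt in".

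**The concern.** The hypothesis is about a proportion and the test is about an amount. An arm can have far more participants without having longer counselling per participant, and the reverse is also possible.

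A lognormal variable is strictly positive. Changing the default acts mainly by moving patients from no post-discharge counselling to some, so the patients at zero carry much of the effect that the hypothesis describes. A method with no place for zeros is a poor match for that outcome.

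At stake is one of the three parts of Hypothesis 1. Depending on how total time is read and how zeros are handled, the same data could give a null result or a strong one, and neither would directly answer whether more patients took part.

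**Working it through.** **Reproducing the plan's figures.** The uptake figures feed the projected quit rates, and these reproduce exactly:
- OPT IN: 0.30 × 0.29 + 0.70 × 0.10 = 0.157
- OPT OUT: 0.80 × 0.29 + 0.20 × 0.10 = 0.252

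The article gives no power or sample size for the counselling comparison.

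**Expected zeros if total time means call minutes.** Arm sizes are 387 OPT OUT and 625 − 387 = 238 OPT IN (the average in the expected scenario), or 500 per arm at the maximum of 1000.
- 238/387: zeros 0.70 × 238 ≈ 167 and 0.20 × 387 ≈ 77, together 244/625 = 39%. Non-zero: about 71 v 310.
- 500/500: zeros 350 and 100, together 45%. Non-zero: 150 v 400.

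**Behaviour of the test.** A t-test on log minutes was simulated, with 1,500 trials per setting. The article does not give a significance level, the spread of minutes or the typical minutes. The following are therefore assumptions: two-sided 5%; SD of log minutes 0.5 to 1.0; median 60 minutes among OPT IN accepters and 45 to 60 among OPT OUT accepters. For scale, four completed calls take about 30 + 3 × 15 = 75 minutes by the article's call lengths. Ranges cover both sets of arm sizes.

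| Participation | Median minutes among accepters (IN v OUT) | Zeros dropped | log(minutes + 1) | Inpatient time added (assumed median 10 min, log SD 0.5) |
|---|---|---|---|---|
| 30% v 80% | 60 v 60 | favours OPT OUT in about 2-3% | favours OPT OUT in 100% | favours OPT OUT in 100% |
| 30% v 80% | 60 v 50 | favours OPT IN in 27-97% | favours OPT OUT in 100% | favours OPT OUT in 100% |
| 30% v 80% | 60 v 45 | favours OPT IN in 60-100% | favours OPT OUT in 100% | favours OPT OUT in 100% |
| 50% v 50% (500/500, log SD 0.8) | 60 v 75 | favours OPT OUT in 87% | favours OPT OUT in 14% | favours OPT OUT in 23% |

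In the first row, mean minutes per randomised patient are 0.80/0.30 ≈ 2.7 times higher in OPT OUT, yet with zeros dropped the test rejects only at its null rate. In the last row participation is identical, yet all three versions favour OPT OUT more often than the 2.5% expected by chance in one direction. So no version is a test of participation.

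**Testing the proportion instead.** At 30% v 80% the difference is 0.50.
- 238/387: standard error √(0.30 × 0.70/238 + 0.80 × 0.20/387) = 0.036; the difference is about 14 standard errors.
- 500/500: standard error √(0.21/500 + 0.16/500) = 0.027; about 18 standard errors.

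Power is above 99.9% in both cases, and 23 patients per arm would already give 95%.

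**The case against.** A reader might infer that the planned test compares only accepters and would tend to favour OPT IN. The documents do not support stating that as fact. Nothing in the article says that zeros are dropped. Total time may include counselling in hospital, which all OPT OUT patients receive and which OPT IN patients receive either as similar counselling or as the brief 5 Rs session. The cost section tracks both inpatient and post-discharge counselling. If inpatient time counts, few or no patients are at zero, everyone is compared, and OPT OUT is favoured in every simulated trial at 30% v 80%. The results in favour of OPT IN need both dropped zeros and assumed shorter calls among OPT OUT accepters. This objection stands.

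Three further points also stand in part. The 30% and 80% figures describe uptake of services as a whole, while OPT IN patients choose counselling and medication separately, so the shares of zeros are approximate. The handling of zeros is a detail that an article may leave to a fuller plan. The mediation analysis of Hypothesis 2 uses a structural equation model, so this test's weakness does not carry over to it.

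What the objection does not answer is the mismatch between hypothesis and test. Table 5 names both the variable and the test, so this is a stated choice and not an omission. Counting inpatient time removes the zeros, but it gives unwilling OPT IN patients positive minutes from the 5 Rs session, so having minutes no longer marks taking part in the counselling on offer. Table 3 labels the counselling outcome as post-discharge, and the durations named for storage are those of calls, which makes the reading with many zeros the more likely one.

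**Conclusion.** The point holds in this form: the counselling part of Hypothesis 1 is a claim about how many patients take part, and the named test does not address it on any reading. That conclusion needs no assumption.

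The lognormal misfit is conditional. It holds if total time means post-discharge minutes, with about 70% and 20% at zero if service uptake stands for counselling uptake. The loss of power to the null rate is conditional on a further step, that zeros are dropped, and on equal minutes among accepters. The exact simulation percentages rest on assumed minutes, spread and significance level.

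The importance is moderate. Counselling is a secondary outcome. Verified abstinence at 1 month, which alone drives allocation and stopping, is analysed separately. The change is worth making because the claim is part of a named hypothesis and a suitable test already stands in the same table.

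**What to change.** In Table 5 and Analyses by aim:

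1. For the counselling part of Hypothesis 1, compare between arms the proportion of all randomised patients who complete at least one post-discharge counselling call, taken from the call log, with a two-sample binomial. State that the inpatient 5 Rs session does not count as participation.
2. State whether total counselling time includes inpatient minutes.
3. Report minutes as a supporting measure over all randomised patients with zeros kept, either as a difference in means with robust or bootstrap standard errors or by a two-part model. Do not use log minutes among patients with any minutes as the hypothesis test.

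The cost is wording. The article already plans to store the number and duration of calls, so no new data collection is needed. Because Analyses by aim restricts Hypothesis 1 to consented patients, the new wording should also say how patients who decline consent at 1 month are counted.

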#### Post-discharge treatment—OPT OUT—medication prescription and NRT “starter pack”

Study staff will work with all patients in OPT OUT to select a long-term cessation medication and plan how they will obtain and fill prescriptions post discharge. Study staff will request a prescription for post-discharge cessation medication via a note in the patients’ medical record, and via a text message to the floor pharmacist assigned to the patients’ medical team. The patients’ hospital physician will make the final determination regarding whether to write a cessation medication prescription, and which medication to prescribe.

To ensure that patients leave the hospital with some form of cessation medication, in order to avoid relapse, study staff will provide all OPT-OUT patients with a 2-week starter pack of over-the-counter quit-smoking medications. This will include 14 days of combination nicotine replacement pharmacotherapy, consisting of 14 nicotine patches plus 14-day supplies of either (a) nicotine gum, or (b) nicotine lozenges. The choice of the short-acting NRT will be made based on contraindications, past history of success/failure, and personal preferences [3]. On the day of hospital discharge, study staff will provide the sealed starter pack to the patient at the bedside, for the patient to use once they leave the hospital.

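### The two-sample Poisson test for days of medication use assumes variance equal to the mean, which the plan's own uptake figures make implausible; for 14 to 28 days among users the standard error is about 2 to 4 times too small

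*Protocol article*

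**What the plan says.** Table 5 of the protocol article, under Hypothesis 1, lists "Medication: treatment condition and number of days of medication use" and names a "2-sample Poisson test" as the analytic strategy. The section on secondary outcomes, mediators and moderators confirms that medication use is summarized as a day count per patient. For Hypothesis 1, Analyses by aim sets the time point at one month and says of the method only: "These analyses will involve two-sample tests". The article states no dispersion term, zero-inflation or robust variance.

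Three other places bear on how the count will be distributed:

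- **Uptake (Projected quit rates).** For OPT IN: "we estimate that 30% of OPT-IN participants will be ready to quit and receive services". For OPT OUT: "we estimate that 80% of patients will accept services".
- **What non-acceptors receive (Inpatient counseling and treatment plan, OPT IN).** "Patients will only receive the elements of care to which they opt in".
- **Supply (Post-discharge treatment, OPT OUT, medication).** "This will include 14 days of combination nicotine replacement pharmacotherapy". A prescription is also requested, and OPT IN patients who want medication are supplied in the same way.

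**The concern.** A count that mixes non-users at zero with users on one to several weeks of treatment has a variance well above its mean. A test that sets the variance equal to the mean then understates the standard error. Hypothesis 1 claims significantly greater medication use in OPT OUT. At stake are the width of the interval reported for that difference and, if the arms turned out to be similar, the false-positive rate of the test.

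**Working it through.** **Inputs from the article.** Uptake p = 0.30 (OPT IN) and 0.80 (OPT OUT). Level-4 and level-1 quit rates are 29% and 10%. The starter pack covers 14 days and assessment is at one month. The maximum sample is 1000, taken as 500/500 at 1:1. In the expected scenario the average is 625, of whom 387 are in OPT OUT, leaving 625 − 387 = 238 in OPT IN.

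**Assumed.** Mean m and variance v of days among users, which the article does not give; uptake of services stands for medication use; two-sided 5% level.

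**1. The plan's own figure.** 0.30 × 0.29 + 0.70 × 0.10 = 0.157 and 0.80 × 0.29 + 0.20 × 0.10 = 0.252. Both match the article, so 30% and 80% are its working uptake values.

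**2. Zeros.** 1 − 0.30 = 70% in OPT IN and 1 − 0.80 = 20% in OPT OUT; pooled at 1:1, (70 + 20)/2 = 45%.

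**3. Dispersion.** Days are 0 with probability 1 − p, otherwise mean m and variance v. The mean is pm and the variance is pv + p(1 − p)m², so

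D = variance/mean = v/m + m(1 − p).

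A Poisson test needs D = 1. The most favorable case for it is v = 0, every user taking the same number of days. At m = 14, D = 14 × 0.70 = 9.8 in OPT IN and 14 × 0.20 = 2.8 in OPT OUT. With v = 0, D falls to 1 only at m = 1/0.70 = 1.4 days in OPT IN and m = 1/0.20 = 5 days in OPT OUT.

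**4. Between-arm contrast.** The squared ratio of true to Poisson standard error is

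- difference in means: Σ(pD/n) / Σ(p/n)
- log rate ratio: Σ(D/(pn)) / Σ(1/(pn))

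At m = 14, v = 0, 500 per arm:

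- Difference: (0.3 × 9.8 + 0.8 × 2.8)/(0.3 + 0.8) = 5.18/1.1 = 4.71, square root 2.17.
- Log ratio: (9.8/0.3 + 2.8/0.8)/(1/0.3 + 1/0.8) = 36.17/4.58 = 7.89, square root 2.81.

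Over both allocations (500/500 and 238/387):

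| Mean days among users (SD) | Difference | Log ratio |
|---|---|---|
| 5 (0–3) | 1.3–1.9 | 1.7–2.2 |
| 7 (0–4) | 1.5–2.2 | 2.0–2.6 |
| 14 (0–9) | 2.2–3.4 | 2.8–3.8 |
| 20–21 (0–8) | 2.6–3.3 | 3.4–3.9 |
| 28 (0–3) | 3.1–3.4 | 4.0–4.2 |

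**5. Type I error.** 4,000 simulated trials per setting, 500 per arm, equal uptake in both arms, Poisson z-test at nominal 5%. Days among users were all 14, Poisson with mean 14, or uniform on 1–14, 1–28 or 14–28. Rejection rates were 46–62% at 30% uptake, 41–56% at 55% and 25–46% at 80%. An unequal-variance z-test on the same data rejected 4.4–5.6% of the time.

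**6. At the projected uptake.** With use uniform on 1–28 days, m = 14.5 and v = 65.25.

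- Difference in means: 0.5 × 14.5 = 7.25 days.
- Arm variances: 0.3 × 65.25 + 0.3 × 0.7 × 14.5² = 63.73 and 0.8 × 65.25 + 0.8 × 0.2 × 14.5² = 85.84.
- Valid SE: √((63.73 + 85.84)/500) = 0.547, z = 13.3.
- Poisson SE: √(14.5 × 1.1/500) = 0.179, z = 40.6.

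Over uniform 1–14 and 1–28, the valid z is 13.3–13.5 at 500/500 and 10.4–10.5 at 238/387.

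**The case against.** The strongest reply is that the size of the error does not come from the plan. No section gives the mean or spread of days among users, and a 14-day pack is a supply, not a record of use. Below about a week of use the factor can fall under 2, and at 14 days with no spread the OPT OUT arm alone is understated only √2.8 = 1.7-fold. This stands: the factor must be stated as conditional on days of use.

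Uptake of services is also only a proxy. The outcome is not limited to study-supplied or post-discharge medication, so inpatient or self-bought nicotine replacement would reduce the zeros. This stands too.

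A third reply is that dispersion is commonly left to an analysis plan that is not shown. This carries less weight, because the article names the test, and a plain Poisson test has no dispersion term.

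A reader might infer three stronger things that the article does not support:

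- **That the data are mostly zeros.** This fits OPT IN (70%) but not OPT OUT (20%) or the pooled sample (45%).
- **That the trial would declare a false difference about half the time.** That requires equal medication use in both arms, whereas OPT OUT provides medication by default and the plan projects 30% versus 80%.
- **That the mediation analysis inherits the error.** Mediation uses Bayesian structural equation modeling, not this test.

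**Conclusion.** The named test does not suit this variable. Given the projected uptake as a proxy for use, the count is overdispersed in both arms unless users take medication for only a few days. The direction of the error therefore needs little assumption, while its size depends on days among users: a factor of about 2 to 4 at 14 to 28 days, and about 1.3 to 2.6 at 5 to 7 days.

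The practical harm is an interval that is too narrow, and a much inflated false-positive rate if the true difference were absent. At the projected uptake a valid test still gives z above 10, so the significance verdict would be the same. The outcome is secondary; the primary abstinence analysis, adaptive allocation, stopping rule and stated power do not use this test. It is worth correcting because the change is cheap, but it does not threaten the trial's main result.

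**What to change.** In Table 5, replace the Poisson test with a comparison of mean days that has a valid variance. Any one of these would do: Poisson regression with robust variance, an unequal-variance test, a permutation test with a bootstrap interval, or a Bayesian hurdle or overdispersed count model. The robust-variance Poisson is the smallest change and keeps the same estimand.

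Apply it in the plan's defined analysis set for Hypothesis 1, which Analyses by aim describes as consented patients. Do not code missing days as zero: the article says it will have no data on patients who refuse consent, and a zero should mean observed non-use.

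Add a two-sample binomial comparison of any medication use. Hypothesis 1 is worded as more patients using medication, which is a proportion that a test of days does not address directly.

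The cost is a short edit to Table 5, a few lines of code, and wider intervals. No new data are needed.
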